**Methods of Intervention**

*Methods for Dealing with Adverse Events*

Study staff will be trained to identify and manage adverse events (e.g., participants becoming mentally distressed, carrying weapons, using drugs and alcohol, or becoming ill). Study staff have attended trainings given by the Maryland AIDS Administration, Baltimore Crisis Response (BCR), and the House of Ruth, a local domestic violence program.

The Lighthouse has established collaborative relationships with a variety of local resources such as local drug treatment, mental health, and other service providers who have facilitated referrals for past Lighthouse study participants. We also maintain an extensive community resource database that is updated several times throughout the year. We work closely with the Johns Hopkins Hospital and the Baltimore Crisis Response (BCRI), a community-based mental health service provider. Individuals who report very high levels of depressive symptoms will be referred to the BCRI. If participants report suicidal ideation or otherwise indicate psychiatric crisis, the interviewer will notify [name] (Co-Investigator) or [name] (Project Director) who will facilitate his/her call to the BCRI for evaluation. Upon participant request, BCRI will send a counselor to evaluate the participant and, if indicated and requested, bring him/her to their facility for emergency residential psychiatric treatment. Drs [name] and [name] will refer questions on the study’s psychiatric emergency cases or protocol to the project’s psychiatrist, [name] (Co-PI), who will be on call for psychiatric issues and emergencies. [name], has developed the mental health crisis protocols for the Lighthouse. All project facilitators and interviewers have received mental health crisis training.

Participants who experience significant distress will be referred to a community-based crisis center, Baltimore Crisis Response (BCR) which is an agency with whom the study investigators have an ongoing relationship. BCR have beds available for referral and trained staff who take phone calls. If unexpected events occur during a focus group or pilot intervention session, group leaders will be trained to work as a team so that as one addresses the immediate concern, the other will continue to lead the group. Group leaders will not be expected to be mental health professionals. Instead, they will be able to identify situations where it is necessary to get help from other trained staff. In mental health emergencies, participants will be referred to clinical staff on site or to clinical care in the community and known to the research team.

**Methods for Dealing with Illegal Reportable Activities**

Participants will be informed that Maryland law requires that cases of child abuse (physical or sexual), reports of harming self or others will be reported to Baltimore City Social Services and/or the Baltimore City Police. The survey does not contain questions about abuse, so it is unlikely that this topic will be broached during the interviews or focus groups. Upon approval of Phase 3 of this study by the JHSPH IRB, we will seek a Certificate of Confidentiality from the National Institute on Drug Abuse.

**Risk/Benefits:**

**Description of Risks**

The researchers will keep the information gathered from participants as confidential as possible, but complete privacy cannot be absolutely guaranteed. There is the potential risk that information shared by a participant during a focus group or pilot group session would be shared outside of the group by another participant. The consent form indicates that information about other participants should not be shared outside of the group, but we cannot guarantee that other intervention participants will keep information that is shared in the groups confidential. Some participants may feel uncomfortable talking in a group setting (i.e. focus groups or pilot sessions) with strangers. In addition, some people may feel guilty, anxious, upset, or depressed because of the information shared by themselves or others.

Enrollment in a group for behavioral intervention involves minimal risk to participants. The voluntary informed consent form and process describe all of the potential risks of study participation. Some participants may feel uncomfortable talking in a group setting with strangers. Participants experiencing significant distress or requesting services will be assisted immediately and referred to the appropriate supportive services. In a health or mental health emergency situation, participants will be referred to clinic staff on site (a psychiatrist on faculty who consults with the project) or to emergency care in the immediate community (e.g. Baltimore Crisis Response). Either the consulting psychiatrist will come to the study site to meet with and assess the client or a trained staff from Baltimore Crisis Response will speak with the client on the phone to assess and make referrals or can send the Baltimore Crisis Response Mobile Team to assess in person. During the consenting process, participants will be informed that 1) cases of child abuse and 2) imminent harm to self or others will be reported to the Baltimore City Police and the Baltimore Department of Social Services as appropriate. The intervention sessions do not contain questions about child abuse, so it is unlikely that this topic will be broached.

Some participants may feel uncomfortable talking in a group setting with strangers. In addition, some people may feel guilty, anxious, upset, or depressed because of the information shared by themselves or others. Some participants who are randomized to the control condition may feel disappointed that they are not able to partake in the full intervention.

**Description of Measures to Minimize Risks**

To minimize risk of breaches of confidentiality, we have taken a number of steps, including: 1) making clear all of the potential risks of study participation during the informed consent procedure and letting participants know during the informed consent procedure that they have the freedom to withdraw from the study at any time; 2) intending to request a Certificate of Confidentiality that will protect the identities of participants in this study forever, even from legal subpoena; 3) not using individual identities in any reports or publications that may result from this research; 4) storing all audio recordings of interviews, focus groups, pilot visits, baseline and follow-up visits, and intervention sessions and quantitative data on a password protected server with firewall; and 5) using unique study numbers on all data collection instruments.

**Description of Potential Benefits**

Few direct benefits to participants are anticipated during Phase 1 and Phase 2. Prior experience suggests, however, that participation in focus groups and pilot intervention sessions is an enjoyable experience for some participants and that many feel good about themselves as a result of helping researchers address issues related to HIV prevention. Referrals to mental health, counseling and other supportive services will be provided, along with printed information about the prevention of HIV transmission to all participants. Finally, some participants may learn tools to help cope with stress or may learn how to change risky behaviors

In Phase 3, the potential benefits will be learning about HIV and mental health. Referrals to mental health counseling, drug treatment, and social services will be available to clients who are in need of these services. Participants who take part in the intervention/control sessions may find the sessions informative and enjoyable. In addition, some participants may learn tools to help cope with stress or may learn how to change risky behaviors

**Description of Level of Research Burden**

Interviews, focus groups, pilot visits, baseline and follow-up interviews, and intervention sessions will be scheduled at times convenient to the participants. The focus groups, interviews, and pilot visits should not take more than 2.0 hours to complete. The baseline and follow-up visits may take up to 2 ½ hours to complete and the intervention sessions will take approximately 90 minutes. Participants are free to withdraw from the study at any time and will be informed of this right during the informed consent statement.

**Compensation:**

**Type of Compensation**

**Phase 3: Full Trial**

Participants will be paid with checks that can be cashed at local check cashing stores.

**Amount of Compensation**

**Phase 3: Full Trial**

Participants will be paid $35 for completion of the baseline and the follow-up visits. In addition, they will be paid $25 for attending each group session.

**Schedule of Compensation**

**Phase 3: Full Trial**

Participants will be paid immediately after completing a baseline, follow-up or intervention/control group session.

**Disclosure/Consent Process:**

**Description of the Consent Process**

In Phase 3, participants will meet individually with a staff member in a private room to go through the informed consent process. The interviewer will read through the consent form with the client.

A participant will be asked if they are willing to provide an oral specimen to test for cocaine and heroin metabolites. They will indicate their willingness by completing a box on the consent form. In addition, they will be asked if they are willing to provide an oral sample to test for HIV. They will indicate their willingness by completing a box on the consent form.

Participants who are interested in participating in the study will also indicate their willingness by signing the consent form.

Before a participant signs the consent form, staff will thoroughly review the form, ask if the participant understands the content of the consent form, allow the participant time to read the consent themselves and answer any questions they may have. Participants will be given a copy of the informed consent form for their records.

**Who Will Obtain Consent**

Interviewers and Group Leaders will obtain consent. All staff have completed the requirement IRB training modules.

**Where and When**

Written consent will be obtained at the beginning of the baseline visit. Consent will be obtained in a private room at the Lighthouse research facility.

**Safety Monitoring:**

A DSMB has been established for this project.

***DMSB Charge or Charter***

The primary responsibility of the project’s DSMB is to safeguard the interest of clients. Therefore, the DSMB have been charged with the following actions:

- Provide review of the protocol and the data safety monitoring plan (DSMP).
- Be available to the Investigator for consultation concerning any adverse study events.
- Review the progress of the study carefully and diligently with special attention to reports of adverse events, drop-outs, or perhaps some other reports generated by group leaders
- Provide a written report to the IRB which summarizes oversight activities and recommendations, and any concerns regarding subject safety.
- Consider the impact of newly published findings bearing on the safety profile of the study.

***Plans for providing DSMB reports to the IRB:*** A brief DSMB report including a summary of their activities will be submitted to the JHSPH IRB when the project annual report is submitted.

***Describe plans for interim analysis and stopping rules.***

Interim analyses of the data will be conducted halfway through the follow-up period (and where virtually all participants will have provided 6-month behavioral interim behavioral endpoints). Interim reports will be prepared for the DSMB by an external statistician; they will be presented to the protocol team blinded as to study arm (Arms will be labeled simply “A”, and “B”,).

If the results show any of the following:

- Increases in the overall number of drug use and risk behaviors for all study participants, as compared to baseline levels, that are statistically significant at the p<.001 level.
- Differences in study outcomes between the control arm and intervention study arm that are statistically significant at the p<.001 level
- Differences in the number of serious adverse events (calculated by collapsing all SAEs based on statistical power assessments) between the control arm and intervention study arm that is statistically significant at the p<.01 level. SAEs include mortality, suicide, suicide attempts, hospitalizations (physical health and mental health or drug-related), and violence.
- Level of depression symptoms (CES-D_) will also be assessed between the two arms to ensure that the experimental intervention does not lead to greater symptomology

Then consideration will be given to stopping the study. When considering whether to stop the study, the overall risks and benefits experienced as of the interim analysis date will be weighed by the protocol team. The recommendation of the DSMB and opinion of the study sponsor will be given heavy weight. In addition, we will track important events and consider appropriate modifications in procedures. We will consult with the DSMB regarding any substantive changes in study procedures.

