***Intervention***

This study will include 1 treatment and 1 control condition. The treatment group is a 10-session skills-building workshop (9 group-based sessions and 1 individual session) based on Cognitive Behavior Therapy. The intervention will focus on developing skills to cope with stress and lower one’s risk for HIV. The intervention group will be led by 2 trained group leaders.

The control group will be a 1 session on standardized HIV information. This session will be led by 1 group leader and last approximately 90 minutes.

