***Follow-up Visits***

Follow-up surveys will be conducted at 6 and 12 months after the intervention. All participants who meet the longitudinal study eligibility criteria will be invited to participate in the follow-up visits. Participants will be informed of these follow-up visits during the informed consent process at the baseline visit. Approximately 1 month before their follow-up date, staff will contact clients through phone calls and letters to remind them of upcoming follow-up assessments. A copy of the reminder letter for each follow-up period is included.

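### Between-arm interim results, masked only by the letters A and B, go to the team still running the trial, and that team weighs whether to stop

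*Protocol*

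**What the plan says.** The Safety Monitoring section of the protocol, under the heading on interim analysis and stopping rules, sets the following.

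- **Timing.** "Interim analyses of the data will be conducted halfway through the follow-up period", when nearly everyone has reached the 6-month assessment. Under Follow-up Visits, "Follow-up surveys will be conducted at 6 and 12 months after the intervention", so a 12-month assessment comes after the look.
- **Author and readers.** "Interim reports will be prepared for the DSMB by an external statistician". Of the same reports it says that "they will be presented to the protocol team blinded as to study arm", the arms being labelled A and B.
- **Content.** One criterion is pooled: a rise from baseline in drug use and risk behaviour across all participants. The other three compare the arms. They are "Differences in study outcomes between the control arm and intervention study arm that are statistically significant at the p<.001 level", a difference in serious adverse events at p<.01, and a CES-D comparison intended "to ensure that the experimental intervention does not lead to greater symptomology".
- **Who weighs stopping.** If a criterion is met, "the overall risks and benefits experienced as of the interim analysis date will be weighed by the protocol team". The DSMB's recommendation and the sponsor's opinion are to carry heavy weight.

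Two other sections bear on the mask. Under Intervention, "The treatment group is a 10-session skills-building workshop", while the control arm has a single session. Under Data Security, survey data and session attendance are entered in a password-protected database open to study staff, investigators, the data manager and data analysts.

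**The concern.** A DSMB supplied by an external statistician normally keeps the interim treatment effect away from the people running the trial. Here the plan sets up that arrangement and then passes the same comparative report to the protocol team, with two letters as the only protection.

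Two things are at stake. First, the outcomes are self-reported risk behaviours and depressive symptoms, and the baseline survey is described as partly interviewer-administered. A team that knows the 6-month effect could, without meaning to, let it influence how follow-up is pursued or how the remaining 12-month data are gathered. Second, a team with an interest in the result weighs stopping on by-arm data it has seen itself, so the DSMB advises on a question the team may already have formed a view on.

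**Working it through.** No stated figure has to be reproduced, because the point concerns who sees what. Most of the check consists of reading the sections against one another. Two small calculations give a sense of size.

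**1. What the letters conceal.** A comparison of A with B shows the size of the difference and its p-value in full. Only the identity of the better arm is hidden.

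**2. Whether the mask fits the task.** The CES-D criterion asks whether the experimental intervention makes symptoms worse. Answering it, or weighing benefit against risk, requires knowing which arm is experimental. If the team is masked, it cannot do the task. If it does the task, it is not masked.

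**3. Whether direction can be recovered from data.** The arms differ by 10 sessions to 1, and attendance and survey data are in a database that investigators and staff can open. Anyone with that access can identify each participant's arm and compute the 6-month contrast, whatever the DSMB report shows.

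**4. Whether direction can be guessed (illustration).** The chance that the better-looking arm is the truly better one is Φ(δ/SE), with SE = SD × √[(2/n) × (1 + (m − 1) × ICC)].

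Inputs from Power calculations: δ = 2.0 CES-D points, m = 8 per cohort, ICC 0 to 0.05, n = 200 per arm. The Population section (about 500 randomised) gives up to 250 per arm; 225 is the midpoint. SD = 8.3 is an assumption, since the protocol calls 8.3 a variance.

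- With n = 225 and ICC = 0.02: SE = 8.3 × √[(2/225) × 1.14] ≈ 0.84, and Φ(2.0/0.84) ≈ 0.99.
- Over n = 200 to 250 and ICC = 0 to 0.05, the probability is 0.98 to 0.996.
- If 8.3 is a variance, SD = √8.3 ≈ 2.88, SE ≈ 0.29, and the probability is practically 1.
- The result depends on the true effect. With SE = 0.84 it is Φ(1.0/0.84) ≈ 0.88 for 1.0 point, Φ(0.5/0.84) ≈ 0.72 for 0.5 point, and 0.50 for no effect.

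So a guess that the better-looking arm is CBT is usually right if CBT works as planned, and uninformative if it does not work.

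**5. How much 12-month data remains (illustration).** The protocol gives no recruitment length. Assume even enrolment and a look when the last participant reaches 6 months. Those enrolled in the final 6 months then still owe a 12-month visit, a share of 6/R for R months of recruitment (R of at least 6).

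| Recruitment, R (assumed) | Share still owing a 12-month visit |
|---|---|
| 12 months | 6/12 = 50% |
| 24 months | 6/24 = 25% |
| 36 months | 6/36 ≈ 17% |

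**The case against.** The strongest defence is that this is a behavioural trial in which staff already know who attends which sessions, that the report is coded, that an external statistician writes it for the DSMB, and that the DSMB's view carries heavy weight. Part of the survey, as described at baseline, is computer self-interview, which limits any interviewer influence.

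Much of this stands as a limit on the point. A reader might infer any of the following, and the protocol does not support them:

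- **That the labels hide nothing.** They do hide direction until someone guesses it or looks it up.
- **That the people doing the 12-month interviews will know the effect.** The protocol team is not defined, and no section puts interviewers or tracing staff on it.
- **That attendance tables in the interim report make identification certain.** The listed criteria cover risk behaviours, study outcomes, serious adverse events and CES-D. Attendance is not among them. The route to the arms is the database.
- **That the sign alone reveals the arms with 99% probability.** That figure presupposes the planned effect and an SD of 8.3.
- **That all 12-month outcomes are exposed.** Groups form whenever about 20 people are eligible, so enrolment is staggered and some 12-month data may already be in.
- **That the DSMB is bypassed.** Its role is advisory, but it is present.

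The defence does not answer the core. Knowing one participant's arm is different from knowing the trial's interim effect, and only the second can be avoided here. No section restricts comparative results to the DSMB.

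**Conclusion.** The point holds as a design weakness that should be corrected. The protocol gives coded between-arm results to the team still running the trial and has that team weigh stopping. The coding leaves every effect size and p-value visible and conflicts with the CES-D criterion. The team can learn the 6-month effect before the remaining 12-month self-reports are in. It does not follow that it will, or that bias will result.

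The number of outcomes affected cannot be fixed from the protocol. The 17% to 50% range rests on assumed recruitment lengths of 36 down to 12 months, even enrolment and the assumed timing of the look. The guessing probabilities are illustrations only. The conclusion rests on the text about who receives the report, who weighs stopping and who can open the database, and would stand without either calculation.

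**What to change.** Amend the interim analysis section in three places.

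1. By-arm interim results, coded or not, go only to the DSMB and the external statistician. The DSMB assesses the three between-arm criteria, knowing which arm is which.
2. The protocol team receives pooled data (recruitment, retention, total serious adverse events and the pooled risk-behaviour criterion) together with the DSMB's recommendation. By-arm results are released to it only if the DSMB recommends stopping or a change.
3. Staff and investigators with database access under Data Security will not run by-arm outcome analyses before the final analysis. Without this, rewording the reporting line alone leaves the database route open.

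The DSMB charge should list review of the between-arm comparisons, since at present it dwells on progress, adverse events and drop-outs. It would also help to say who makes up the protocol team and whether interviewers are included.

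The cost is a few sentences and an internal rule on database use, with no added visits or participants. The small downside is that the protocol team sees less at the interim.

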**Confidentiality Assurances:**

***Certificate of Confidentiality (if applicable)***

Upon approval from the JHSPH IRB of Phase 3 of the study, we will seek a Certificate of Confidentiality from the National Institute on Drub Abuse.

***Data Security***

All participants who consent to participate in the Phase 3 will be assigned a unique identifier. Their survey data, locating information, which will be collected electronically, and information regarding sessions that they attend will be entered into a password protected database that is located on a secure internal server. Study staff, Investigators, Data Manager and Data Analysts will have access to the database. We will use this information to track the participants for reminder calls for follow-up visits and to exclude participants from future screening and duplicate enrollment in the full trial phase. The locating data files will be destroyed by the Data Manager 6 months after the study is over.

Digital audio-recorded interviews, focus groups, pilot visits, baseline, follow-up surveys, and intervention sessions will be verbally labeled with the date of visit and participant’s unique study ID number. These data files will be saved on a password protected computer with firewall server and labeled with the date and number of the focus group. These recordings will be deleted by the Data Manager within 1 year after the study ends. During the focus groups, pilot group sessions, and full trial group sessions, participants will be asked to use only their first names when identifying themselves. Attendance lists will collect only the first names and last initial of participants as a way to monitor attendance and attendance information will be entered into the participant database immediately after the intervention and the paper form will be destroyed.

